### Participant timeline

The first administration of rfhSP-D will be given as soon as possible after administration of standard-of-care surfactant therapy, this will be known as T0. Subsequent administration will be given at T0+12 (±2) hours and T0+24 (±2) hours. Eligibility and screening investigations will be done before each administration of the IMP as shown in the schedule of events table 1.

**Table 1 T1:** Schedule of events at screening and prior to administration of the IMP

Study visit	Screening	Baseline	Preinstillation of IMPT0	Preinstillation of IMPT0+12 hours (±2 hours)	Preinstillation of IMPT0+24 hours (±2 hours)
Informed consent	*				
Eligibility	*				
Clinical stability		*	*	*	*
Demographics (including gestational age (GA))	*	*			
Pregnancy and delivery history		*			
Stabilisation history		*			
Clinical assessment (anomalies)	*				
Vital signs	*	*		*	*
Oxygen concentration	*	*		*	*
Ventilator modality		*		*	*
Ventilator settings		*		*	*
Haematology (as per standard of care)		*			*
Biochemistry (as per standard of care)		*			*
Cytokine levels (plasma)		*			*
Cell counts GA/ETA		*		*	*
Surfactant replacement	*				
Plasma SP-D and rfhSP-D levels		*		*	*
Blood gases	*	*		*	*
SP-D levels GA		*			
rfhSP-D and SP-D level ETA				*	*
Concomitant medication		*		*	*
Cranial ultrasound scan		*			*
Review of AEs and SAEs (from time of consent)		*	*	*	*

Standard of care refers to blood samples that are taken as part of clinical care and not specific to the study.

*refers to events that must be done as per the schedule of events.

AEadverse eventETAEndotracheal AspirateGAGastric AspirateIMPinvestigational medicinal productSAEserious AESP-Dsurfactant protein D

Further clinical data will be collected as per the time points outlined in table 2 schedule of events.

**Table 2 T2:** Subsequent time points in participant timeline following IMP administration

Study visit	T0+36 hours(±6 hours)	T0+48 hours(±4 hours)	T0+72 hours(±12 hours)	T0+96 hours(±12hours)	T0+7 days(±2 days)	T0+14 days (±2 days)T0+21 days (±2 days)T0+28 days (±2 days)	36 weeks PMA (±1 day)	40 weeks PMAor hospital discharge (±1 week)
Vital signs	*	*	*	*	*	*	*	*
Oxygen concentration	*	*	*	*	*	*	*	*
Ventilator modality	*	*	*	*	*	*	*	*
Ventilator settings	*	*	*	*	*	*	*	*
Haematology (SoC)		*	*	*	*			
Biochemistry (SoC)		*	*	*	*			
Plasma cytokine levels		*	*	*	*		*	
Plasma SP-D and rfhSP-D		*	*	*	*		*	
Blood gases		*	*	*	*	*	*	
ET cell counts	*	*	*	*	*			
ETA rfhSP-D and SP-D levels		*	*	*	*		*	
Concomitant medication	*	*	*	*	*	*	*	*
Cranial ultrasound scan		*			*	*	*	*
Walsh oxygen test							*	
Review of AEs and SAEs	*	*	*	*	*	*	*	*

*refers to events that must be done at these timepoints.

AEadverse eventETAendotracheal aspirateIMPinvestigational medicinal productSAEserious AESoCstandard of careSP-Dsurfactant protein D

The RESPONSE study will collect clinical data and biological specimens (blood, tracheal and gastric aspirates) as per tables1  2. Parents/guardians/those legally responsible for the participant will have the option to give consent for any anonymised data and samples that are collected as part of RESPONSE to be used in other ancillary studies that have ethical approval. Gastric secretions will be taken from all infants at the time of admission after placement of oro/nasogastric tube and will be discarded if consent is not obtained. Blood samples (0.5 mL of blood in an EDTA microtainer) will be collected at birth, 12 hours, 24 hours, 48 hours, 72 hours, 96 hours, day 7 and at 36 weeks PMA. Given the risk of anaemia and associated comorbidities in the study population, if there are any clinical concerns about anaemia, the clinical stability of the infant or the participant is receiving a blood transfusion the blood samples for SP-D and cytokine analysis will either be delayed or not taken.

### Data collection and management

Participants once recruited to the RESPONSE study will be allocated a study number so that all data and samples that are taken are anonymised, for example, RES_001. Participation in the clinical study will be recorded in the participant clinical records. Participants will be enrolled by the study team on the OpenClinica database. Participant clinical and laboratory data will be entered directly into the password-protected study database. After completion of the trial, the data will be exported and retained in restricted folders by the sponsor. All data will be held for 10 years following the completion of the trial.

Primary outcome data collection in this study (safety profile of rfhSP-D) will be done through grading and analysis of the incidence of DLEs. Potential causality of the DLE to the IMP will be assessed by an independent neonatologist. In addition to the DLEs, the following datasets will be collected from electronic patient records:

At screening and on eligibility assessment: sex of participant, ethnicity, maternal medical history, antenatal steroid courses, date and time of rupture of membranes, concerns about maternal sepsis, ventilatory requirement on admission and administration of standard exogenous surfactant.

Secondary outcome data collection:

Data will also be collected at the time points specified in the schedule of events (tables2  3) and this will include concomitant medication, ventilatory support and parameters, known positive microbiology, use of postnatal steroids, presence and treatment of pulmonary hypertension, pneumothorax, patent ductus arteriosus, use of postnatal steroids.At 36 weeks, PMA all participants will be assessed for severity of BPD and data will be collected about complications of prematurity such as episodes of necrotising enterocolitis and retinopathy of prematurity. The severity of BPD in participants will be defined as per the 2019 National Institute of Child health and Development (NICHD) criteria,^36^ an oxygen reduction test will be done if the participant is eligible (requiring less than Fi02<0.3 or 1.1 L/min and not on positive pressure support) and remains an inpatient at the recruiting site.

**Table 3 T3:** Operating characteristics of the continuous reassessment model

Starting dose level 1, dose-skipping not allowed, 3 dose levels, maximum 24 participants.Skeleton (a priori probabilities of DLE) = 0.05, 0.11, 0.20target DLE rate=no greater than 20%			
	Dose level		
	1	2	3
Scenario 1: recommendation (%)	2.5	24.5	73.0
Scenario 2: recommendation (%)	22.5	46.5	31.0
Scenario 3: recommendation (%)	0.0	3.3	96.7
Scenario 1: true probabilities=a priori probabilitiesScenario 2: true probabilities=0.10, 0.20, 0.30Scenario 3: true probabilities=0.02, 0.05, 0.10			

DLEdose-limiting event

All data will be handled in accordance with the Data Protection Act 2018 and General Data Protection Regulation (GDPR) and all study members will have current GCP training and certification.

### Analysis of biological samples

Biological samples will be collected as per the schedule of events. Samples will be labelled with the participant’s study number and transported to the Targeted Lung Immunotherapy Laboratory, UCL. Surfactant components, inflammatory markers and level of SP-D will be analysed using the ELISA technique (ELLA, BioTechne) with single marker studies and multiplex assays. Cytokines to be analysed include IL-1β, IL-6, IL-8, IL-11, IL-10, IL-13, matrix metalloproteinase-9 and tumour-necrosis factor-α. Cell counts (lymphocytes, neutrophils and macrophages) in gastric and tracheal aspirates will be assessed using flow cytometry. Samples will be retained if consent has been given by the parent/legal guardian for 5 years for use in any other ethics-approved studies. If consent is not given for use in further studies or at the end of 5 years, the biological samples will be destroyed as per the laboratory standard operating procedure.

### Sample size and statistical analysis

As this is a safety study, no formal sample size calculation has been performed. A sample size of 24 infants is planned to meet practical recruitment and time targets and to collect sufficient data to quantify the estimated risk of DLE at each dose level. Participants with unclear safety outcomes or who have not started study treatment will be replaced to meet our planned effective sample size of 24 participants.

The primary outcome of interest is the occurrence of DLEs at the dose levels under investigation and the identification of the dose(s) that, for infants of particular risk profiles defined by GA, have an estimated risk of DLE closest to the target side effect level of no greater than 20%. The use of Bayesian methodology to estimate risks will allow information to be borrowed across dose levels, making the dose-escalation and RP2D identification procedure more efficient than a standard rule-based approach.

The operating characteristics of the design, for three specific scenarios, are shown in table 3. The first scenario is one where the initial a priori DLE probabilities calculated by calibration (halfwidth of the indifference interval set at 0.05) correspond to the true underlying probabilities of DLE. The second scenario is such that the true DLE rate of the second dose level corresponds to the target DLE rate. The third scenario is one where the true probabilities are much lower than the a priori probabilities.

Type and grade of DLEs, SAEs and AEs will be tabulated per dose level, and further summarised by risk group defined by GA. Mean estimated risk of DLE per dose level and 95% credibility intervals will be calculated using the study model. Secondary objectives will be described per dose level and risk category. Categorical variables will be summarised by frequencies and percentages, and continuous variables by means/medians and SD/IQRs per dose level.

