**Figure 1 F1:**
[figure not shown]
Dose escalation process in RESPONSE using rfhSP-D in preterm infants at risk of BPD. *Via Endotracheal tube only. **First iteration will be at 1mg/kg/dose, subsequent iterations 2 mg/kg/dose and 4 mg/Kg/dose. ***Neonatal Adverse Event Severity Score (NAESS). ****administration window of +2 hours. BPD, bronchopulmonary dysplasia; DLE, dose-limiting event; DSMB, data and safety monitoring board; TSC, trial steering committee.

The three dose levels to be considered are 1 mg/kg/dose, 2 mg/kg/dose and 4 mg/kg/dose. Participants will be enrolled at each dose level with a minimum of three participants per dose level. Each participant will receive three doses of rfhSP-D at 0 hours, 12 hours and 24 hours provided that they continue to meet the inclusion criteria and are clinically stable. The first dose of rfhSP-D should be administered after standard surfactant therapy has been given. Whether or not the dose level is escalated will depend on the occurrence of DLEs in all current participants and the doses they have received. A model will be used to estimate the risk of DLE per dose level. Initial estimates of these risks will be updated using data collected throughout the trial. A one-parameter empiric model will be used to describe the relationship between the dose and the probability of observing a DLE. The CRM model will not allow dose-skipping. The target level of DLEs level is set at no greater than 20%. Before the trial, the parameter of the model will be assigned a non-informative prior distribution and initial estimates of DLE probabilities will be derived using model calibration. The recommended phase 2 dose will be defined by considering safety and will be the highest dose level that has an estimated probability of DLE closest but below the target DLE level of no greater than 20%.

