#### Dose escalation procedure

A schema of the dose escalation procedure and review is shown in figure 2. The sentinel baby is the very first baby recruited to the study and this baby must be greater than 26 weeks GA. The sentinel baby must have received all three administrations of the IMP and have had 72 hours of observed data post administration of third administration before further infants can be recruited for the study. If the first participant does not receive all three doses of the IMP then data will still be collected but they will not qualify as the sentinel baby for this study. All infants recruited after the sentinel baby will be from 23 weeks to 29 weeks and 6 days GA for the remainder of the study. A data and safety monitoring board (DSMB) review of the Neonatal Adverse Event Severity Score (NAESS) data will take place after each infant (for the first three participants at each dose level) has received the final dose of IMP and 72 hours of monitoring. The DSMB will evaluate the safety data before further participants can be recruited, that is, the second or third baby cannot be recruited until data from the first or second baby has been reviewed. This will only be for the first three infants at each dose level, thereafter the data will be reviewed in cohorts of three unless there are safety concerns. Following the recruitment of three infants at any dose level all safety data will be reviewed by the DSMB and they will then advise the Trial Steering Committee (TSC) before a decision is made to (a) move to next dose level or (b) to stay at the same dose level or (c) decrease the dose level or (d) stop the trial. The final decision on dose escalation will be made by the TSC.

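### The per-dose 95% intervals come from the one-parameter dose-escalation model, so they depend on the skeleton's shape and can under-cover if the true dose-risk curve is flatter

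*Protocol article*

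**What the plan says.** Under Study objectives, the first primary objective is the safety profile across three dose levels, based on the occurrence of DLEs. Under Sample size and statistical analysis, 24 infants are planned partly "to collect sufficient data to quantify the estimated risk of DLE at each dose level", and the precision statement is: "Mean estimated risk of DLE per dose level and 95% credibility intervals will be calculated using the study model".

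The study model is defined under Trial design: "A one-parameter empiric model will be used to describe the relationship between the dose and the probability of observing a DLE". On the prior, "the parameter of the model will be assigned a non-informative prior distribution"; no variance is given. The skeleton in Table 3 is 0.05, 0.11, 0.20, obtained by calibration with the "halfwidth of the indifference interval set at 0.05".

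The same statistical section says that borrowing across dose levels is intended, and that type and grade of DLEs will be tabulated per dose level. It mentions no interval based on a dose level's own data. Table 3 gives recommendation percentages for three assumed curves and says nothing about interval coverage.

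**The concern.** A one-parameter CRM is built to locate a target dose. It does so by holding the relation between the dose risks fixed and letting one parameter move them all together. That suits escalation. It is less suitable as the only precision statement for each dose separately, because the interval at a lightly used dose reflects mainly the assumed shape and the data from other doses.

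The shape assumption may fail here. The Dose-limiting events section counts grade 3 or higher events and SAEs that are only possibly related to the product. In ventilated infants of 23 to 29 weeks, background morbidity attributed in this way could occur at much the same rate at every dose, giving a curve flatter than the skeleton. None of the Table 3 scenarios is of that kind. At stake is whether a nominal 95% interval, published for a first-in-human product and carried into the phase 2 study the article foresees, means what a reader will take it to mean.

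**Working it through.** **Inputs from the protocol.** Empiric model; skeleton 0.05/0.11/0.20; target 20%; half-width 0.05; design settings as in Table 3 ("Starting dose level 1, dose-skipping not allowed, 3 dose levels, maximum 24 participants"); cohorts of 3 (Dose escalation procedure: "thereafter the data will be reviewed in cohorts of three unless there are safety concerns").

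**Assumptions, not in the protocol.** Normal prior on b with mean 0 and variance 1.34 (varied below); next dose is the one whose plug-in estimate is nearest 20%; no early stopping unless stated; the off-skeleton curves.

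**Step 1: reproduce the plan's figures.** Calibration with target 0.20, half-width 0.05 and prior target dose at level 3 gives 0.049/0.110/0.200, the stated skeleton. Simulated recommendation percentages (10,000 runs) against Table 3:

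| Scenario | Simulated | Stated |
|---|---|---|
| 1 | 2.4/24.6/73.1 | 2.5/24.5/73.0 |
| 2 | 21.7/47.9/30.5 | 22.5/46.5/31.0 |
| 3 | 0.1/2.4/97.5 | 0.0/3.3/96.7 |

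All agree within 2 points, so the assumed settings are a fair stand-in for the design.

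**Step 2: what one parameter implies.** The model is p_d = s_d^exp(b), with s_d the skeleton value. Every limit at level 1 is therefore a fixed function of the limit at level 3: L1 = L3^k, with k = ln 0.05 / ln 0.20 = 2.996/1.609 = 1.861. A true curve fits the model only if ln p_d / ln s_d is the same at each dose:
- Scenario 2: 0.77/0.73/0.75. Scenario 3: 1.31/1.36/1.43. Both are close to constant.
- Flat 10%: 0.77/1.04/1.43. No single value fits.

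**Step 3: coverage of the model's 95% intervals, levels 1/2/3.**

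| True curve | Coverage (%) | Truth above level 1 upper limit |
|---|---|---|
| Scenario 1 | 96/96/96 | about 1% |
| Scenario 2 | 96/96/95 | about 3% |
| Scenario 3 | 86/86/84 to 97 | about 12% |
| 0.10/0.12/0.15 | 73/84/80 | 27% |
| Flat 10% | 55/83/70 to 78 | 44% |
| Flat 15% | 61/74/63 | 37% |

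Repeat simulations moved the level 1 figures for the flat curves by about two points. The ranges at level 3 arise because, with no DLE in the trial, the upper limit there is about 0.0996 against a true 0.10, so small numerical differences decide whether it counts as a miss.

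**Step 4: sensitivity to the prior.** At variance 0.56 or 4, level 1 coverage stays at 54 to 55% (flat 10%) and about 60% (flat 15%). Scenario 3 behaves differently: its shortfall disappears at variance 0.5. With the 90% stopping rule applied, Scenario 2 coverage is about 92% at each level.

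**Step 5: one concrete data set.** No DLE in 3, 3 and 18 infants. The model's upper limits are 1.4%, about 4% and about 10%. The first follows from the third: 0.0996^1.861 = 0.014. Over prior variances 4 to 0.5, the level 1 limit runs from 0.7% to a little over 2%. The exact limit from level 1 alone is 1 − 0.025^(1/3) = 0.708, and from level 3 alone 1 − 0.025^(1/18) = 0.185. The model thus states the risk about seven times more tightly (10/1.4) at the dose given to 3 infants than at the dose given to 18. Such an allocation is realistic: Scenario 3 averages about 3.5, 4.1 and 16.4 infants per level.

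**Step 6: the model-free comparator.** Exact intervals covered 95.8% to 99.9% on every curve tried. Their mean widths in Scenario 1 are 0.64/0.58/0.47, against 0.16/0.24/0.30 from the model.

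**The case against.** The strongest reply is that the plan is coherent. Borrowing across doses is stated openly, model-based intervals are ordinary CRM output, DLEs are also tabulated per dose, and a statistical analysis plan that is not shown could add a model-free summary. Anyone holding the counts can compute an exact interval. All of this is true, and it limits the point to how a stated precision figure is presented. It does not change where the protocol says that figure comes from.

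A reader might infer from the flat-curve results that the reported intervals will be wrong, or wrong mostly on the unsafe side. The documents do not support that. Coverage is nominal in Scenarios 1 and 2. The Scenario 3 shortfall comes from the roughly 12% of trials with no DLE at all and depends on a prior variance the protocol does not give. The flat curves are assumptions, and both flat rates lie below the 20% target, so a miss there does not mean that an unacceptable dose was passed. With a flat 15% risk, level 1 receives on average about 9.6 infants, so the misses reflect the wrong shape more than a small number at that dose.

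The 71% comparator is also not a rival best estimate. It ignores 21 event-free infants at higher doses; pooling all 24 gives an exact upper limit of 1 − 0.025^(1/24) = 14%. It shows how much of the 1.4% comes from the model. Whether the exact interval should replace the model interval as the main statement is debatable; showing both is enough.

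**Conclusion.** The concern holds in a limited form. The stated per-dose intervals are conditional on the skeleton's shape. They are about nominal if that shape is right. If the true curve is flatter, level 1 coverage can fall to roughly 55% to 73% for the three flatter curves tried, and the prior variance hardly alters this. The design settings are supported by the close reproduction of Table 3; the prior variance and the flatter curves remain assumptions. A flatter curve is plausible under the protocol's DLE definition but not established.

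The consequence is for reporting the first primary objective. Nothing here argues against using the CRM for escalation or for choosing the RP2D. It is a worthwhile and inexpensive improvement, and it does not invalidate the design.

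**What to change.** Keep the CRM for escalation and the RP2D. In the statistical analysis section:
- Beside each CRM mean and 95% credible interval, report the number of infants treated, the number with a DLE, and an exact (Clopper-Pearson) or Jeffreys 95% interval from that dose level's own data. Name the method in advance.
- Label the CRM interval as conditional on the one-parameter model and its skeleton.
- Reword the rationale for 24 infants so that it does not imply dose-by-dose precision independent of the model. For example: the sample supports model-based estimation of DLE risk across the dose range, and precision from the data at any single dose will be limited.

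The cost is one extra table column and a sentence or two. The added intervals will be wider and look less favourable, about 0.6 against 0.2 at level 1. Recruitment, dose decisions and interim reviews are unaffected.

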#### Interim analyses of DLEs

Interim analysis will done to assess if DLEs have occurred after each infant (for the first three participants at each dose level) has received the final dose of IMP and 72 hours of monitoring and all NAESS data will be reviewed by the DSMB. The DSMB will evaluate the safety data before further participants can be recruited, this will only be for the first three infants at each dose level. The purpose of this is to ensure there are no safety concerns. For the remainder of the study, interim analysis will be done after cohorts of three participants are recruited at any dose level to assess the occurrence of DLE and review all clinical data. Overall DSMB review of all data to advise the TSC regarding dose escalation will take place after recruitment of 3 infants at any dose level. The trial statistician will calculate and provide updated summaries of the estimated risk of dose-limiting toxicity at each dose level. The DSMB will then advise if dose escalation can occur. There will be no interim analysis for the secondary outcomes.

The study will be terminated if any of the following stopping rules are satisfied:

There is at least a 90% chance that the risk of DLE at dose level 1 is greater than the target of 20%. If the trial is terminated under this rule, no drug dose will be recommended due to safety concerns.The number of participants who have been treated without side effects is deemed sufficient.There is evidence of increased mortality or morbidity in the participants treated with the IMP.

### Study oversight and monitoring

The sponsor will provide trial oversight and verify the trial processes and prompting corrective action to the clinical study team as required. An independent TSC will provide oversight of the trial to safeguard the interests of the trial participants. The TSC will also provide advice to the chief investigator, CCTU and the funder on all aspects of the trial through its independent chair. An independent DSMB is assigned with an allocated chair. The DSMB will be responsible for monitoring and accumulating the safety data and making recommendations to the TSC on whether the trial should continue as planned. The DSMB will consider data as per the statistical analysis and make recommendations to the TSC chair for consideration by the TSC.

